### Assessment tools

To assess HRQL, the Short-Form-36 Health Survey (SF-36) will be used. For a more specific assessment on respiratory issues, the Saint Georges Respiratory Questionnaire (SGRQ) will be used. Both questionnaires have been validated in Spanish.

To evaluate ICU stressors, the ICU Stressful Experience Questionnaire (ICU-SEQ) will be used. This tool was created by Rotondi and modified by Samuelson. In addition to evaluating general ICU experiences, it also evaluates experiences related to the endotracheal tube.

To translate and adapt the ICU-SEQ into Spanish, the following process will be used:Translation and back translation into Spanish by two bilingual translators.Transcultural adaptation via a pilot study to assess proper comprehension of the different items.

Details of the assessment tools and data collection schedule are summarized in Table 2

**Table 2 Tab2:** Measurement tools

Tools	Assessment Area	Dimensions	Items	Score
SF-36	Health-Related Quality of Life (general)	Physical sphere, social sphere, Physical role, Emotional role, mental health, vitality, pain, general health (8)	36	Every item of each dimension (8 in total) will be codified, aggregated and turned into a scale, with values that range from 0 till 100 (rating each health-related dimension from worse to best)
QRSG	Health-Related Quality of Life (respiratory)	Symptoms, activity, impact (3)	50	Each item has a specific weight assigned on the global score. Scores can range from 0 till 100 (rating quality of life from minimal to maximal alterations).
ICU-SEQ	ICU Stressors	No dimensions as such, but 2 very differentiated areas: ICU stressors in general and airway related stressors.	31	It’ll be assess if the patient remembers anything, and if so, assessment of stress’s perception will be performed (range of values: none, very little, Some, Quite a bit, A lot)

SF-36: Medical Outcome Study-Short Form 36, QRSG: Saint Georges Respiratory Questionnaire, ICU-SEQ: ICU Stressful Experience Questionnaire

.

### Data collection

Data will be collected over 12 consecutive months. Patient selection for the study cohort will be performed by the research team by evaluating all patients who may need or had needed MV. Follow up documentation will be provided for all mechanically ventilated patients. When a patient has been mechanically ventilated for over 48 h, informed consent will be obtained from the next of kin. From that moment, all patient data from their medical records will be gathered until MV is discontinued.

One week after the patient has been discharged from the ICU, informed consent will be obtained from the patient. Approaching the patient earlier is considered to be inappropriate by the research team. If the patient agrees to participate in the study, the SF-36, SGRQ and ICU-SEQ questionnaires will be provided for the patient to complete. The same questionnaires will be given to the main caregiver at that time. One year after ICU discharge, the same questionnaires will be completed again to assess the persistency of stressors’ sequelae.

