## Methods/design

### Aims

#### Main objective

To assess health-related quality of life of mechanically ventilated patients admitted in an ICU and its relation to nursing-sensitive outcomes.

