#### Secondary objectives

To determine whether there are any differences in HRQL in mechanically ventilated patients prior to admission into ICU and one year after discharge from the ICU.To identify whether there is any relationship between the duration (in days) of mechanical ventilation and HRQL one year after discharge from the ICU.To identify whether there is any relationship between NSO and HRQL of mechanically ventilated patients one year after discharge from the ICU.To identify differences between the patient’s own assessment of HRQL and the main caregiver’s perception.To identify stressors that mechanically ventilated patients admitted in ICU identify when discharged and which ones last for at least one year after they have left the ICU.To identify whether there is a relationship between the amount and type of stressors perceived by mechanically ventilated patients during their admission and their HRQL one year after discharge from the ICU.

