### Variables

The following variables will be collected: anthropometric and sociodemographic data and data related to ICU admission, mechanical ventilation, NSO, HRQL and ICU stressors. Variable definitions and the data collection schedules are summarized in Table 1

**Table 1 Tab1:** Variables and Measurement Schedule

Category	Variables	Measurement Schedule
Anthropometric	Age, Gender	Admission
	Weight, Height	Admission and 12 months after ICU discharge
Sociodemographic	Academic level	Admission and 12 months after ICU discharge
	Employment, economic income	
	Main caregiver, family/social support system	
ICU length of stay	Main medical diagnosis, reason for ICU admission, APACHE II, Age corrected Charlson Index	Admission
	ARDS, MODS, Surgical interventions, blood transfusion, renal replacement therapy, Ramsay Score for >3 hours.	Daily
	Complications, GCS, Barthel Index, length of ICU stay (days) and hospital stay	ICU discharge and 12 months after
		ICU discharge and hospital discharge
Mechanical Ventilation	Reason for intubation and MV	Admission
	Modes of MV utilised (hours and days)	Daily
	Respiratory complications	
	Days with tracheostomy tube in place	ICU Discharge
	Days on MV	
NSO	Total hours in pain (Assessed using a VAS), PU, Falls, VAP, CRB, UTI	Daily
	Allocated nurse’s expertise	
HRQL	SF-36, QRSG	ICU discharge and 12 months after
	SF-36, QRSG (assessed by main caregiver)	ICU discharge
ICU Stressors	ICU-SEQ	ICU discharge and 12 months after

APACHE II: Acute Physiologic A Chronic Health Evaluation II, ARDS: Acute Distress Respiratory Syndrome, MODS: Multiorgan Dysfunction Syndrome, GCS: Glasgow Coma Score, ETT: Endotracheal Tube, MV: Mechanical, VAS. Visual Analog Scale, PU: Pressure Ulcers, VAP: Ventilator Associated Pneumonia, CRB: Catheter Related Bacteriemia, UTI: Urinary Tract Infection, SF-36: Medical Outcome Study-Short Form 36, QRSG: Saint Georges Respiratory Questionnaire, ICU-SEQ: ICU Stressful Experience Questionnaire

.

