### Data analysis

A descriptive analysis will be carried out for all variables. Mean and standard deviation will be utilised for quantitative variables that follow a normal distribution. For the rest of the variables, the median, maximum and minimum values will be used. Qualitative variables will be described utilising absolute frequencies and percentage values for each category.

Statistical analysis of HRQL results will be performed on the questionnaire’s different dimensions as well as on the questionnaire as a whole. To compare the results obtained at the time of ICU discharge with those obtained one year after discharge, Student’s t-test or Wilcoxon test will be applied to the paired data depending on the variable distribution. This analysis will also depend on the length of MV.

A multiple regression model will be elaborated utilising HRQL as the result variable. Relevant clinical situations (number of transfusions and surgical interventions, pressure ulcers, nosocomial infections…) will be considered as independent variables. All analysis will be performed with a 95 % confidence interval.

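### The only stated stop for the daily nursing-sensitive outcomes is the end of ventilation, so events between ventilator removal and ICU discharge are not captured

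*Protocol article*

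**What the plan says.** The Data collection section ties record abstraction to ventilation at both ends. It begins after consent: "When a patient has been mechanically ventilated for over 48 h, informed consent will be obtained from the next of kin". It then states that, from that point, "all patient data from their medical records will be gathered until MV is discontinued".

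Table 1 (Variables) lists the NSOs as "Total hours in pain (Assessed using a VAS), PU, Falls, VAP, CRB, UTI". Their schedule is daily, and no last day is given. In the same table, "Complications, GCS, Barthel Index, length of ICU stay (days) and hospital stay" are scheduled at ICU discharge or later, and days with a tracheostomy tube at ICU discharge.

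The main objective is "To assess health-related quality of life of mechanically ventilated patients admitted in an ICU and its relation to nursing-sensitive outcomes". A secondary objective treats ventilation length as an exposure of its own: "To identify whether there is any relationship between the duration (in days) of mechanical ventilation and HRQL one year after discharge from the ICU".

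On the model, Data analysis says: "Relevant clinical situations (number of transfusions and surgical interventions, pressure ulcers, nosocomial infections…) will be considered as independent variables". The Methods paragraph of the Abstract adds that variables on ICU length of stay, ventilation, stressors and NSOs will enter a multiple regression on quality of life.

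**The concern.** NSOs are the exposure in the main objective, so the period over which they are counted defines that exposure. The stop rule closes the count when the ventilator is removed, although the patient may stay in the ICU for days and can still fall, develop a pressure ulcer or an infection, or be in pain.

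Two things are at stake. First, a patient whose only event comes in that later period may be treated in the regression as having had none. Second, the time over which NSOs can be seen becomes ventilation time by construction, so two patients with the same event history can be classified differently only because one was ventilated for longer. Events that were never abstracted cannot be restored by any later analysis. The Limitations section does not mention this.

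**Working it through.** **Plan's own figure.** There is none to reproduce. The document gives no split of the ICU stay into ventilated and later days, no NSO rate and no effect size.

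**Passages side by side**

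| Item | Stated timing | Place |
|---|---|---|
| Record data in general | Stop when ventilation ends | Data collection |
| NSOs | Daily, no end day | Table 1 |
| Complications, length of ICU stay | ICU discharge or later | Table 1 |
| Tracheostomy days | ICU discharge | Table 1 |
| NSOs as exposure | Ventilated ICU patients, no limit to ventilated days | Main objective |

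The Table 1 items due at ICU discharge cannot all be completed if abstraction has already closed, so the two places disagree for those items. For the NSOs, Table 1 sets no competing end, and the Data collection rule governs by default.

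**Share of ICU time outside the window.** Counting from the start of ventilation, with M ventilated days and P further ICU days:

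share omitted = P / (M + P)

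M and P are assumptions (M from 4 to 14, P from 1 to 7).

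- M = 14, P = 1: 1/15 = 7%
- M = 10, P = 4: 4/14 = 29%
- M = 4, P = 7: 7/11 = 64%

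Under a constant daily event rate, also an assumption, this is the expected share of events missed for an NSO that can occur on any ICU day. Ventilator-associated pneumonia is tied to ventilation by definition and falls outside this calculation.

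**Patients with at least one event.** A simulation assumed mean ventilation of about 10 days, constant rates of 0.01 and 0.03 events per day, and a post-ventilation stay unrelated to ventilation length.

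| Mean further ICU days | Patients with any ICU event who are captured | Correlation of observation time with ventilation days: current rule | Same, window to ICU discharge |
|---|---|---|---|
| 2 | 84–85% | 1.00 | 0.97 |
| 4 | 72–75% | 1.00 | 0.89–0.90 |
| 7 | 61–65% | 1.00 | 0.75 |

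**How far NSO status and ventilation days overlap.** In the same simulation, having any NSO correlates with ventilation days at 0.22 to 0.32 under the current rule and 0.16 to 0.29 with a window to ICU discharge. At 0.32, the two-variable variance inflation is 1 / (1 − 0.32²) = 1 / 0.898 = 1.11. The longer window loosens the tie but does not remove it, and the loss of precision is small either way. Cumulative measures such as pain hours could correlate more strongly; no figure was computed for them.

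**The case against.** The strongest reply is that this is a loose sentence, not a chosen design. Table 1 plainly expects staff to return to the record at ICU discharge, and its undefined complications item might pick up some late events. This stands in part: it is wrong to say that all record collection ends with ventilation. But complications are listed apart from the NSOs, and an abstractor who follows the sentence would stop the daily NSO entries early.

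Several stronger readings are tempting, and the documents do not support them:

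- **That NSO effects and ventilation effects cannot be separated.** The Abstract places ventilation and ICU-stay variables in the same regression as NSOs, and the overlap computed above is modest.
- **That NSO effects are diluted towards zero.** This would need classification error unrelated to the outcome. Here the error depends on ventilation length, itself a candidate determinant of quality of life, so the direction is open.
- **That a known fraction of events is lost, or nearly all falls.** The document gives nothing from which to derive either.
- **That late events are coded as absent.** No coding rule is stated. The risk is that patients are treated as unexposed by default.
- **That Table 1 already sets ICU discharge as the end for NSOs.** It gives them no end day.

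Nor does this argument bear on the start of collection, which the article places after next-of-kin consent. Analysing NSOs per day at risk instead of as totals is a modelling preference, since total burden may be the exposure of interest.

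**Conclusion.** The point holds in a limited form. The stop rule conflicts with the Table 1 items due at ICU discharge, and it cuts NSO capture short of the period that the main objective covers. The loss concerns pressure ulcers, falls, pain hours, catheter-related bacteraemia and urinary infection. Some exposed patients may be analysed as unexposed, and NSO observation time is tied to ventilation length.

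The size and direction of the bias cannot be derived from the document. The 7% to 64% of ICU days omitted, and the 61% to 85% of patients with an event who are captured, rest on assumed stays and constant event rates. They show only that the loss could be anything from minor to substantial.

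The correction should be made, but this is not a fatal flaw. The description of quality of life and the comparisons over time, with caregivers and of stressors do not depend on the NSO window.

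**What to change.** 1. In Data collection, move the stop for the daily variables from the end of ventilation to ICU discharge, and give the daily NSO row of Table 1 the same end point so that the two agree.
2. Record the date of each NSO, so that events during and after ventilation can be told apart.
3. Keep ventilation days and ICU length of stay in the regression beside the NSOs, as the Abstract already indicates, and say so in Data analysis.

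The cost is a short amendment and a few more days of chart abstraction per patient, from records already in use. The first two changes must be in place before abstraction; the third can be made at the analysis stage.

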### Data analysis

A descriptive analysis will be carried out for all variables. Mean and standard deviation will be utilised for quantitative variables that follow a normal distribution. For the rest of the variables, the median, maximum and minimum values will be used. Qualitative variables will be described utilising absolute frequencies and percentage values for each category.

Statistical analysis of HRQL results will be performed on the questionnaire’s different dimensions as well as on the questionnaire as a whole. To compare the results obtained at the time of ICU discharge with those obtained one year after discharge, Student’s t-test or Wilcoxon test will be applied to the paired data depending on the variable distribution. This analysis will also depend on the length of MV.

A multiple regression model will be elaborated utilising HRQL as the result variable. Relevant clinical situations (number of transfusions and surgical interventions, pressure ulcers, nosocomial infections…) will be considered as independent variables. All analysis will be performed with a 95 % confidence interval.

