**Methods:**

Prospective longitudinal cohort study in which all patients admitted to the ICU at *Hospital Universitari Vall d’Hebron* who undergo MV for more than 48 h will be included. The study will last 12 consecutive months. HRQL will be assessed by the completion of the SF-36 and the Saint Georges Respiratory Questionnaire. Pre-admission HRQL assessment will be performed by the main caregiver, and after ICU discharge, the assessment will be performed by the patient him/herself. The same questionnaires will also be completed one year after ICU discharge. Other variables (sociodemographic and those related to reason for ICU admission, ICU length of stay, MV, ICU stressors and NSO) will be included in a multiple regression model to assess their relation to the patient’s HRQL.

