Being able to identify which factors negatively influence a patient’s HRQL, whether they are certain invasive therapies (MV or renal replacement therapies) or the stressful ICU environment, should allow us to establish proactive strategies that will prevent or diminish the occurrence of physical or psychological sequelae. It would be very beneficial to implement measures to prevent the onset of anxiety, post-traumatic stress disorder or depression, as well as establishing early rehabilitation programmes, instead of waiting for these disorders to appear. It is very important to know each therapeutic action’s specific impact in order to implement specific strategies during both the acute and later phases of the process, so adverse events resulting from therapeutic interventions as well as ICU-generated stress could be minimised, always taking into account the patient’s own perception during the decision-making process. This project will allow us to determine the perceived HRQL one year after discharge from ICU and compare it with that measured earlier on in the process, as well as analyse the negative experiences they had while in the ICU as a result of MV and their impact over time. It will also allow us to assess the effect of NSO and ICU stressors on health-related outcomes and how they affect HRQL. This study could highlight the importance of early nursing interventions, in both acute and later phases of the process, in order to minimise some of the sequelae and improve patient welfare.

It could also be useful to understand the concordance between the HRQL perceived by patients and main caregivers to understand the patient’s own motivations regarding his health process.

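### Secondary objective 1 asks about change since before ICU admission, but the only before-after test named starts from ICU discharge

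*Protocol article*

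**What the plan says.** All references are to the protocol article.

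- **Secondary objectives.** The first item concerns "differences in HRQL in mechanically ventilated patients prior to admission into ICU and one year after discharge from the ICU".
- **Data analysis.** One before-after comparison is described, opening "To compare the results obtained at the time of ICU discharge with those obtained one year after discharge". The method is a Student's "t-test or Wilcoxon test will be applied to the paired data depending on the variable distribution".
- **Abstract, Methods.** "Pre-admission HRQL assessment will be performed by the main caregiver, and after ICU discharge, the assessment will be performed by the patient him/herself".
- **Table 1 (Variables).** The patient's SF-36 and respiratory questionnaire are scheduled at ICU discharge and at 12 months. The caregiver's version is scheduled at ICU discharge only. No quality-of-life row is labelled pre-admission.
- **Data collection.** "One week after the patient has been discharged from the ICU, informed consent will be obtained from the patient", and consenting patients then receive the questionnaires. For the caregiver: "The same questionnaires will be given to the main caregiver at that time". No reference period is given for either form.
- **Discussion.** One-year quality of life will be known, and the authors will "compare it with that measured earlier on in the process". The earlier time point is not specified.

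**The concern.** The objective and the test have different starting points. One asks whether patients at one year differ from how they were before the critical illness. The other, read literally, asks whether they differ from how they were around ICU discharge. The patient's first form is completed about a week after leaving the ICU, following more than 48 hours of ventilation, so change from that point describes recovery. If it were reported as the answer to objective 1, improvement since discharge could be taken for a return to, or gain over, the pre-admission state.

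The article does not leave this comparison to another document. It states one, with its time points and test, and those time points do not match the objective.

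**Working it through.** The plan gives no effect size, standard deviation or power for this comparison, so there is no figure to reproduce. The check sets the contrasts side by side.

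**Notation** (one scale): P = pre-admission score as the patient would rate it; C = caregiver's rating of the pre-admission state; D = patient's score about one week after ICU discharge; Y = patient's score at one year.

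**Contrast that objective 1 asks for:** Y − P.

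**Reading A: the discharge value is the patient's form.** The test estimates

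Y − D = (Y − P) + (P − D).

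It differs from the objective by P − D, the change between pre-admission and the discharge visit. On the SF-36, where higher is better, the sign differs whenever D < Y < P. On the respiratory questionnaire, where higher is worse, it differs whenever P < Y < D. Table 1 favours this reading, because only the patient's form has both a discharge and a 12-month entry.

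**Reading B: the discharge value is the caregiver's form, describing pre-admission status.** The test estimates

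Y − C = (Y − P) + (P − C).

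The starting point is now right, but P − C, the difference between self-rating and proxy rating, is added. Secondary objective 4 treats that difference as an open question of its own, and the Discussion makes the usefulness of the proxy conditional on concordance.

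**Does another analysis fill the gap?** The regression uses quality of life as outcome and lists clinical events as predictors. The list is open-ended, but no pre-admission score is named in it. The descriptive analysis covers all variables, so the caregiver scores would be summarised, but no test or interval for pre-admission versus one year is named.

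**Illustration only (SF-36 direction; every mean and SD assumed).** Take P = 70, D = 35, Y = 58.

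- Reading A: 58 − 35 = +23.
- Objective 1: 58 − 70 = −12.

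With the expected final cohort of 200 as complete pairs and an SD of paired differences of 25, the 95% half-width is 1.96 × 25 / √200 = 3.5 points (2.8 for SD 20, 4.2 for SD 30). A recovery contrast could thus be estimated precisely without bearing on objective 1. The opposite signs come entirely from the chosen means: with Y = 75 the two contrasts would be +40 and +5, the same sign.

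**The case against.** The strongest defence is that the pre-admission value is itself obtained at the discharge visit. The abstract assigns pre-admission assessment to the caregiver, and the caregiver's form is handed out at that visit. The Data analysis section identifies results by when they were obtained, not by the period they describe, so the planned test may be objective 1 loosely worded. The Limitations section names patient memory as the main bias, which is compatible with retrospective answers, though it may refer only to ICU stressors. This reading is possible. It does not rescue the plan, because the analysis text never says which of the two forms is paired, and Reading B brings in the rater difference.

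A second defence is that a condensed article need not map each test to an objective, and that a discharge-to-one-year comparison is useful in itself. The latter is true, and the comparison should stay. The article nowhere says that this test will be reported as the answer to objective 1, so the harm is conditional on that use.

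A reader might go further and infer any of the following. The documents do not support them:

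- *The pre-admission value is not used at all.* It falls under the descriptive analysis; what is missing is a named inferential comparison.
- *The discharge score is at the low point, so the conclusion will be reversed.* No scores or reference periods are given that would establish this.
- *The pre-admission form is already scheduled, so only the analysis paragraph needs rewording.* That rests on the abstract alone; Table 1 and Data collection give no form a pre-admission reference period.

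**Conclusion.** The point holds as a mismatch between a stated objective and the stated contrast. Followed as written, no named test clearly addresses secondary objective 1. On Reading A the test measures change since ICU discharge, which can differ in size, and possibly in sign, from change since before admission. On Reading B it mixes change over time with a proxy-versus-self difference.

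The size of either discrepancy cannot be derived from the article. A sign reversal is possible but not shown. The conclusion rests only on the wording of the objectives, Table 1, Data collection and Data analysis, and on taking the abstract at its word that the caregiver supplies the pre-admission assessment. Because this is a secondary objective of an observational cohort and the wording is partly ambiguous, it should be fixed but does not undermine the study as a whole.

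**What to change.** 1. **Data analysis.** Name the caregiver-reported pre-admission score versus the patient's 12-month score as the paired analysis for objective 1, per scale, with mean paired difference and 95% confidence interval, or the Wilcoxon test where the distribution calls for it.
2. **Table 1 and Data collection.** State the rater and reference period of each form, giving the caregiver's form an explicit pre-admission reference period in line with the abstract.
3. **Interpretation.** Report the objective 1 result as subject to the proxy-versus-self difference, and read it alongside the patient-caregiver comparison of objective 4. That comparison isolates the rater difference only if both forms describe the same period, which is a further reason to state the period for the patient's first form.
4. **Recovery.** Keep the patient's discharge versus 12-month comparison under its own label as a description of recovery, and say that it does not answer objective 1.

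**Cost.** A few sentences, a little more analysis, and a permanent proxy caveat on the objective 1 result. If the caregiver's form is not in fact given with a pre-admission reference period, its instructions must also change before data collection; rewording the analysis afterwards could not supply the missing baseline.
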